### Economic analysis methods

Data will be collected to estimate intervention costs and examine the feasibility of calculating cost-effectiveness alongside a definitive full pragmatic randomised trial. Health care service use will be costed using national unit costs [42, 43]. Both arms of the study with be costed, revisiting and revising the costing methodology used in previous economic analysis of the Welsh NERS [44].

The additional costs of the intervention will consist of the cost of the MWK; staff costs relating to the MWK (e.g. training, implementation and participant follow-up support); the cost of the professional web cloud (e.g. licence fee) and additional staff interactions. These costs are in addition to the core programme costs (in both arms) including NERS standard practice costs and participant contributions. Information about the additional staff resources required for the use of the MWK and professional web cloud will be derived from qualitative interviews with staff.

### Data analysis

#### Quantitative analysis

The main outcomes in this feasibility study are related to the study progression criteria as outlined in Table 4. The methods of analysis for quantitative data collected for the process evaluation are summarised in Table 5. Analyses will be largely descriptive, with summary statistics being presented overall and also by key demographics. Evidence of whether the intervention could lead to behaviour change will be examined using regression analyses to quantify effects on autonomous motivation, using the Relative Autonomy Index derived from the BREQ-3.

To examine the direction of effect on physical activity, analysis of covariance models [ANCOVA] will be used to estimate intervention effects on physical activity at 16 months. Whilst likely non-significant due to limited power, this should be in the direction of a favourable intervention effect. Accelerometer data will be processed using standard procedures; periods of ≥ 60 min of zero counts will be recorded as “non-wear time” and removed. Participants will be included in the analysis if they provide ≥ 3 valid days (i.e. 500 min of data between 6 am and 11 pm). Mean minutes of daily moderate to vigorous intensity activity will be estimated using a threshold value of ≥ 2020 counts per minute with minutes of light intensity physical activity estimated using thresholds of between 100 and 2019 counts per minute [35]. Sedentary time will be estimated based on a cut-point of less than 100 counts per minute; mean sedentary minutes per day will be derived.

#### Qualitative analysis

Qualitative data from interviews with exercise professionals and intervention participants will be transcribed verbatim and organised and coded into a thematic framework using NVivo 11 software. An approach to thematic analysis will be used that allows for both a deductive and inductive approach to data analysis [45]. Data will be initially coded using an a priori coding scheme of categories which align with the research questions as a means of organising the data for subsequent interpretation. An element of flexibility will be maintained to account for the emergence of any new and unexpected themes. The first three transcripts will be independently coded by two coders in order to develop a shared codebook via consensus. Any disagreements between coders will be discussed with a third coder. Divergence and convergence between interviews will be examined and comparisons made of the experiences of the intervention across and within areas (NERS clients and exercise professionals). We aim to develop a comprehensive understanding of the intervention acceptability, implementation and mechanisms of impact.

#### Economic analysis

A pilot cost-consequence analysis will be conducted from a NHS and societal perspective. Response rates and level of completion of the measures will be reported using descriptive statistics. Variables will be checked for out of range values before analysis begins. As data are expected to be skewed, non-parametric tests will be used to assess differences across groups or time points for the outcomes of QALYs (using the EQ-5D) and health and social care service use. We will bootstrap (5000 replications) differences in cost and outcomes to produce a 95% confidence interval around these differences. Ceiling effects on the EQ-5D will also be assessed, assessing the proportion of participants that state “no problems” on all five dimensions on the EQ-5D questionnaire. QALY gains (using the EQ-5D) will be compared to those in similar samples from previous literature (where available).

A report on the data gathered about service use (from routinely collected data recorded by healthcare professionals delivering NERS) will explore if future studies could use this or a different method to the CSRI questionnaire used in the feasibility study. Descriptive statistics will be used to describe the amount participants are willing to pay for the MWK, both during the intervention and beyond. Response rates and level of completion of the questions exploring how best to capture productivity losses will be reported using descriptive statistics.

Sub-group analyses will explore the effect on health-related quality of life of socio-demographics (e.g. gender) and reason for referral. Sensitivity analysis will be conducted in accordance with NICE guidelines to vary the cost of the device [46], demonstrating what happened in the feasibility trial and how co-ordination may be varied in a future full-scale trial.

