**Methods/design:**

The PACERS study consists of a pilot randomised controlled trial, process evaluation and exploratory economic analyses. Participants will be recruited from the generic pathway of the Welsh NERS and will be randomly assigned to receive the intervention or usual practice. Usual practice is a 16-week structured exercise programme; the intervention consists of an accelerometry-based activity monitor (MyWellnessKey) and an associated web platform (MyWellnessCloud). The primary outcomes are predefined progression criteria assessing the acceptability and feasibility of the intervention and feasibility of the proposed evaluation methodology. Postal questionnaires will be completed at baseline (time 0: T0), 16 weeks after T0 (T1) and 12 months after T0 (T2). Routinely collected data will also be accessed at the same time points. A sub-sample of intervention participants and exercise referral staff will be interviewed following initiation of intervention delivery and at the end of the study.

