### The intervention

The intervention is an enhanced ERS that includes usual care (NERS standard practice) [6] plus an accelorometry-based activity monitor (MyWellnessKey; MWK). The MWK can be used for self-monitoring of physical activity levels in combination with a linked web platform (MyWellnessCloud) and smartphone application (see Table 2). The MWK has been validated in terms of device accuracy at monitoring physical activity level and intensity [32, 33] and utility at fostering increased physical activity levels (high concurrent validity with ActiGraph accelerometer to detect physical activity in laboratory and free-living environments) [34].

**Table 2 Tab2:** Features of the MWK activity monitor and MyWellnessCloud web platform

• Real-time visual feedback via a screen on the activity monitor	
• Detailed feedback on activity levels via a web platform to indicate progress towards goals, time spent in different activity intensities and calories burned	
• Automatised goal setting via an algorithm which sets goals in a stepwise fashion such that forward progression is mastery-based	
• Facilitation of social support for exercise via the web platform (through involvement in group challenges and remote communication with an exercise professional) and smartphone app (the option to share details about activity completed via social media)	
• Free access to the web platform and smartphone application following discontinuation of use of the MWK via manual input or by linking the account to another monitoring device.	

Intervention participants will be provided with a MWK to use for the remaining 12 weeks of their 16-week NERS programme after receiving it at their 4-week consultation and will be encouraged to use it for 36 weeks after they exit the scheme, up until their 12-month consultation when the device will be returned. In current practice, conducting an 8-month telephone consultation to check clients’ progress with exercise is an optional part of standard care. To encourage participants to maintain engagement in the study, we have asked for the telephone consultation to take place with all intervention participants. Table 3 shows how the intervention will be implemented within the scheme.

**Table 3 Tab3:** Implementation of the intervention components

Time point	Exercise professionals	Intervention participants

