#### Economic evaluation outcome measures

The PACERS study questionnaire will include an adapted Client Service Receipt Inventory (CSRI) based on the previous service use questionnaire used in the NERS evaluation [7] and examples in the DIRUM database (dirum.org) to capture client health and social care service use since the last time point (plus a 4 month retrospective period at baseline). Additional questions in the 12-month questionnaire will capture wider economic outcomes including current work status, days off work due to health problems and estimated income lost due to changes in work during the study period. Willingness to pay for the MWK will also be explored. Baseline demographic data on housing status and household income will also be collected in the PACERS study questionnaire for the purpose of the economic analysis.

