### Data collection

Routinely collected data will be extracted from the NERS database at all T0, T1 and T2. The PACERS study questionnaire will be mailed to participants at all time points. Telephone and email reminders will be made to non-responders. Semi-structured telephone interviews will be conducted with a sub-sample of intervention participants (*n* = 20) following receipt of the intervention at 4 weeks and again at 12 months (T2) to explore feasibility and acceptability of the intervention and study methods. In addition, telephone interviews will be conducted with a sample of NERS exercise professionals at the same time points to explore feasibility and acceptability of implementing the intervention and study methods from a professional perspective. Figure 3 indicates the schedule of enrolment, interventions and assessments.

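### Service-use recall windows of about 17, 16 and 36 weeks, and QALYs accrued over 16 and 36 weeks, are to be compared across time points with no common period stated

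*Protocol article*

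**What the plan says.** Three statements in the protocol article bear on this point.

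- **Recall.** Under Economic evaluation outcome measures, the adapted Client Service Receipt Inventory (CSRI) is meant "to capture client health and social care service use since the last time point (plus a 4 month retrospective period at baseline". Under Data collection, "The PACERS study questionnaire will be mailed to participants at all time points", so a service-use total is obtained at T0, T1 and T2.
- **Timing.** The Abstract (Methods/design) places the questionnaires at "baseline (time 0: T0), 16 weeks after T0 (T1) and 12 months after T0 (T2". The section on the intervention gives the length of the later interval: participants "will be encouraged to use it for 36 weeks after they exit the scheme, up until their 12-month consultation".
- **Test.** Under Economic analysis, "non-parametric tests will be used to assess differences across groups or time points for the outcomes of QALYs". The sentence covers two outcomes, as it continues "for the outcomes of QALYs (using the EQ-5D) and health and social care service use".

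The EQ-5D-5L comes from routine NERS data at the same three time points (Measures collected routinely in NERS), not from the CSRI. The article nowhere converts service use or QALYs to a rate or to a common period.

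**The concern.** A service-use total grows with the length of time it covers. The T2 total covers more than twice the time of either earlier total. A paired test of totals involving T2 would therefore respond to window length even if nobody's use had changed, and a real fall in use after scheme exit could be masked.

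QALYs raise a related but separate problem. A QALY is utility accumulated over an interval, so its size depends on the spacing of the EQ-5D assessments. It is not a quantity measured at a time point, and no follow-up interval ends at baseline. The outcome named does not fit the comparison named.

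What is at stake is the pilot's description of service use and health-related quality of life over time. The last study objective includes the feasibility of the economic evaluation methods, so this is worth settling before a full trial takes over the same instrument and analysis.

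**Working it through.** **Inputs.** T1 = 16 weeks; T2 = 12 months, taken as 52 weeks; baseline look-back = 4 months (Abstract; Economic evaluation outcome measures).

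**The article's own figure.** 52 − 16 = 36 weeks from T1 to T2. This reproduces the 36 weeks given in the section on the intervention (36.2 weeks if a year is 365.25 days).

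**Recall windows.**
- T0: 4 × 365.25 / 12 / 7 = 17.4 weeks
- T1: 16 weeks
- T2: 36 weeks

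**Ratios of expected totals when the rate of use is constant** (expected total = rate × window, so the rate cancels).
- T2 / T1 = 36 / 16 = 2.25
- T2 / T0 = 36 / 17.4 = 2.07
- T1 / T0 = 16 / 17.4 = 0.92

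Conversely, a true halving of the rate after T1 gives 0.5 × 2.25 = 1.13, so the T2 total would still be slightly above T1.

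**QALYs at constant utility u** (interval QALY = u × weeks / 52).

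| u | T0–T1 | T1–T2 |
|---|---|---|
| 0.6 | 0.18 | 0.42 |
| 0.7 | 0.22 | 0.48 |
| 0.8 | 0.25 | 0.55 |
| 0.9 | 0.28 | 0.62 |

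The ratio is 36/16 = 2.25 in every row. The utilities are assumed values; the ratio does not depend on them.

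**What a signed-rank test would do with the totals.** The article gives no contact rates, so these are assumed: individual rates constant over time, gamma-distributed with mean 2, 4 or 8 contacts a year and shape 0.5, 1 or 2; Poisson counts; 100 or 200 completers (286 × 0.7 = 200 under the article's 30% attrition); 300 runs per setting; paired Wilcoxon signed-rank test at 5%.

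| Comparison, with no true change | Runs significant |
|---|---|
| T1 against T2, totals | 99.7–100% |
| T0 against T1, totals | about 6–27% |
| T1 against T2, counts per week | about 3–9% |

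The last row shows that rescaling brings the error rate back to roughly its nominal level. At a true 5% the Monte Carlo standard error is √(0.05 × 0.95 / 300) = 1.3 percentage points.

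**The case against.** The strongest reply is that the article never says unscaled totals will be tested. It is a condensed account, and a statistical analysis plan that is not shown may convert CSRI responses to rates. The phrase about groups or time points is loose and names no contrast with T2. A sensible analyst might read it as EQ-5D scores over time and QALYs between groups.

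Much of this stands. A reader might infer that the plan commits to testing raw totals; it does not, and the false rise is conditional on that reading. A reader might also infer a rise at every step; but T1 against baseline is close to level and would fall slightly. The simulation adds little to the ratio of 2.25, because its contact rates are assumed.

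The reply does not remove the point. The article itself fixes the recall rule, the outcomes and the comparison, and taken together they do not give a valid comparison with T2. For QALYs, scaling is not the only issue: the outcome named has no baseline value, and its interval amounts reflect the spacing of assessments.

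**Conclusion.** The point holds for time-point comparisons that involve T2. If recall totals are compared, T2 would be about 2.25 times T1 and 2.07 times baseline with no change in use. Interval QALYs differ 16:36 at constant utility, for a separate reason: the spacing of the EQ-5D assessments. Both results rest only on the nominal timings in the article.

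Further consequences that a reader might infer are not supported:

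- **Costs.** The planned non-parametric tests cover QALYs and service use. Cost differences are to be bootstrapped, and no time-point contrast is stated for them.
- **Comparisons between arms.** Both arms share the same window, so these are unaffected.
- **Progression and sample size.** No criterion in Table 4 uses service use or QALYs, and the sample size does not depend on them.
- **Suitability of the CSRI.** The article looks at response, completion and routine data as an alternative source. It does not say that the time-point test informs this.
- **Recall anchoring.** The questionnaire is not shown, so nothing can be said about whether it prints a reference date.

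This is a real flaw of moderate weight in an exploratory analysis, and it is nearly free to correct.

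**What to change.** In the Economic analysis section:

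1. State that CSRI service use is divided by the number of weeks covered, giving a rate per unit time, before any comparison across time points.
2. Name EQ-5D utility, not QALYs, as the outcome compared across time points.
3. Keep QALYs for the comparison between arms over the same 12 months.

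This changes wording and derived variables only; no new data are needed. The downside is that a rate based on 36 weeks of recall carries more recall error than one based on 16 weeks. Rescaling does not cure that, and the report should note it.

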#### Measures collected routinely in NERS

Data collected routinely within NERS will be obtained for use within the trial from T0, T1 and T2, as follows:Blood pressure and resting heart rate;Body mass index;Waist circumference;Self-reported physical activity (Scottish Physical Activity Questionnaire) [36];Health-related quality of life (EQ-5D-5L) [37]; andFitness test (Chester fitness test) [38].

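### The non-parametric test planned for QALYs does not target the mean difference and cannot use the baseline EQ-5D-5L; a bootstrapped, baseline-adjusted mean difference would serve better

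*Protocol article*

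**What the plan says.** The Economic analysis section of the protocol article sets the frame: "A pilot cost-consequence analysis will be conducted from a NHS and societal perspective". It then gives a reason, "As data are expected to be skewed", and the method that follows from it: "non-parametric tests will be used to assess differences across groups or time points for the outcomes of QALYs (using the EQ-5D"). The same sentence extends the tests to a second outcome, "and health and social care service use". The next sentence adds an interval: "We will bootstrap (5000 replications) differences in cost and outcomes to produce a 95% confidence interval around these differences". It names no covariates and rules none out.

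The EQ-5D-5L is listed under Measures collected routinely in NERS, where the timing is given: "Data collected routinely within NERS will be obtained for use within the trial from T0, T1 and T2". T0 is baseline, T1 is 16 weeks and T2 is 12 months. The section on economic outcome measures adds service use from an adapted CSRI, which at baseline looks back 4 months. Under Randomisation, allocation is 1:1 and follows completion of the baseline measures.

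**The concern.** A cost-consequence analysis sets mean incremental costs beside mean incremental outcomes. Skew affects how one obtains a trustworthy interval for a mean. It does not change the quantity wanted. The usual two-sample non-parametric tests ask whether values in one arm tend to exceed those in the other, which is a different question. The plan already has a tool that copes with skew while keeping the mean as target, namely the bootstrap. As written, the report would carry a p-value and an interval that answer different questions and may point different ways.

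Such a test also has no place for a baseline covariate. Baseline utility is part of the QALY area itself and usually predicts later utility, so it is the covariate most worth using. What is at stake is the precision and readability of the pilot QALY estimate, and whether the pilot rehearses the analysis that a definitive trial would need.

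**Working it through.** **The plan's own figure, and the number of completers.** No figure is stated for the QALY comparison. The Sample size section gives 286 participants, for 80% power at the 5% level (taken as two-sided), effect size 0.4 and 30% attrition.
- Normal approximation: n per arm = 2 × (1.96 + 0.8416)² / 0.4² = 98.1, so 99.
- With the t distribution, 99 per arm gives power 0.7997 and 100 per arm gives 0.8036, so 100 are needed.
- 100 / 0.70 = 142.9, so 143 per arm, or 286 in total. The stated figure reproduces and is not affected by this point.

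I therefore use 100 completers per arm below.

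**QALY weights.** With utilities at 0, 16 and 52 weeks and the trapezoid rule:
- w0 = ½ × 16/52 = 0.154
- w1 = ½ × (16/52 + 36/52) = 0.500
- w2 = ½ × 36/52 = 0.346

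**Assumptions.** The documents give neither a utility SD nor correlations. I take equal SDs at the three times (0.25, range 0.20 to 0.30) and a common correlation r of 0.5 to 0.8.

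**How much of a chance baseline difference reaches the QALY difference.** The slope is w0 + r(w1 + w2).
- r = 0.5: 0.154 + 0.5 × 0.846 = 0.577
- r = 0.8: 0.154 + 0.8 × 0.846 = 0.831

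The standard error of the baseline difference is 0.25 × √(2/100) = 0.0354. An imbalance of one standard error therefore moves an unadjusted QALY difference by 0.0204 (r = 0.5) to 0.0294 (r = 0.8).

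**Standard error of the QALY difference.** In units of the utility variance, the QALY variance is

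V = (w0² + w1² + w2²) + 2r(w0w1 + w0w2 + w1w2) = 0.3935 + 0.6065r.

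After adjustment for baseline it is V − slope². Each standard error is 0.0354 times the square root.

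| r | V | slope² | SE unadjusted | SE adjusted |
|---|---|---|---|---|
| 0.5 | 0.697 | 0.333 | 0.0295 | 0.0213 |
| 0.8 | 0.879 | 0.690 | 0.0331 | 0.0154 |

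Both columns scale with the SD. At SD 0.20 they are 0.0236 and 0.0171 (r = 0.5), and 0.0265 and 0.0123 (r = 0.8). At SD 0.30 they are 0.0354 and 0.0256, and 0.0398 and 0.0184. The proportional reduction does not depend on the SD: 1 − √(0.364/0.697) = 28% at r = 0.5 and 1 − √(0.189/0.879) = 54% at r = 0.8. If r were 0 there would be almost nothing to gain (0.0222 to 0.0215 at SD 0.25).

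**Test against mean.** A simulation drew lognormal data with 100 per arm and log-SDs of 1.0 and 1.5, and applied the Mann-Whitney test at 5%.
- Equal means: rejected in 92% of runs.
- Equal medians, means 1.65 and 3.08: rejected in 5% of runs.

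This is deliberately extreme and is not a model of QALYs. It shows only that the test and the mean difference can part company in both directions.

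**The case against.** The strongest reply is that the plan already contains most of the remedy. A bootstrap interval for differences, read in the usual way as differences in means, addresses the right quantity, and the test is a supplement beside it. This stands: the objection is to the test and does not reach the whole economic analysis. The article says non-parametric without naming a test, so a rank test is the likely reading but not the stated one.

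Several stronger readings are tempting, and the documents do not support them.
- **That costs are tested this way too.** The tests cover QALYs and service use. Cost receives only the bootstrap interval.
- **That the bootstrap is of unadjusted differences.** The article is silent. A condensed article may leave covariates to a fuller plan, and the article does name baseline adjustment for the accelerometer outcome. The same holds for the planned "regression analyses to quantify effects on autonomous motivation, using the Relative Autonomy Index derived from the BREQ-3": nothing there excludes the baseline score.
- **That chance imbalance biases the result.** Under randomisation an unadjusted difference is unbiased, and its interval already reflects baseline variation.
- **That EQ-5D data will be lost differently by arm because they come from NERS consultations.** The 12-month consultation is planned for all participants, controls included, and no figure points to differential attendance.
- **That the QALY difference decides progression.** None of PC1 to PC5 in Table 4 uses QALYs or costs.

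What the reply does not remove is that the article states a method for QALYs, and in its standard form that method neither targets the mean nor accepts the baseline covariate.

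**Conclusion.** The point holds in a limited form. The stated between-group test for QALYs is the wrong instrument for an incremental outcome, and it adds a second inference that can conflict with the planned bootstrap interval. A baseline-adjusted mean difference would answer the intended question with a standard error lower by roughly 28% to 54%, given a common correlation of 0.5 to 0.8 and equal SDs. The absolute figures rest further on an assumed SD and 100 completers per arm. They measure adjusted against unadjusted estimation of the mean. They would not be a gain over the bootstrap if that were already to be run on adjusted differences. The benefit is precision and less error conditional on the imbalance that happens to occur.

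Severity is low, because the analysis is an exploratory pilot. It is still worth settling, since testing the feasibility of the economic evaluation methods is among the study's stated objectives.

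**What to change.** Remove the between-group non-parametric test for QALYs. Estimate the mean QALY difference by linear regression on arm and T0 utility, refit the model in each of the 5000 bootstrap samples, and report the estimate with its 95% confidence interval. Treat the mean cost difference in the same way, with cost from the 4-month baseline CSRI period as covariate. The tests of service use can stay as descriptive support.

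The cost is a change of wording and a few lines of code. Nothing new is collected, and adjusting for T0 utility loses no one from the QALY analysis, because a trapezoid QALY already needs that value. Adding the EQ-5D-5L to the T1 and T2 mailings would be an optional safeguard against missed consultations, at the price of about a page in each. The point does not depend on it.
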